## 2. OBJECTIVES

To undertake a comprehensive comparative evaluation of the HPV-specific immune responses against oncogenic HPV types induced when adolescent female subjects are vaccinated with either Cervarix™ or Gardasil™, by

- (i) examining the levels of antibody-mediated cross-neutralisation elicited to oncogenic HPV types following vaccination with either Cervarix™ or Gardasil™
- (ii) comparing the levels and patterns of cross-neutralisation induced by each vaccine to highlight potential differences in immunogenicity between the vaccines
- (iii) assessing whether there are differences in the specificity of mucosal antibodies or cell-mediated immune responses elicited by each vaccine

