#### **E. Randomisation**

A computerised block randomisation list will be produced by the Statistician at Cfl. Each VRN will be allocated blocks of sequential numbers in accordance with the block size used for randomisation. On recruitment to the study, each subject will be allocated, in order of inclusion, the next available study number by their VRN. The study number will define the group to which the subject is assigned and therefore the vaccine they will receive. Vaccinated individuals, however, will not be aware of which HPV vaccine (GardasilTM or CervarixTM) they will be receiving during the course of the study. Laboratory staff will be aware of the study number and patient initials associated with the collected samples but will not be able to link these data with the vaccine received nor other patient identifiers.

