### **Brief description.**

The primary purpose of this study is to determine the level of neutralising antibody reactivity (i.e. antibodies able to prevent HPV infection of target cells in laboratory culture) against not only the vaccine-incorporated types (HPV 16 and 18) but also the genetically-related, non-vaccine cancer-causing types (31, 33, 35, 39, 45, 52, 58, 59, 68). The main outcome will be the proportion of vaccinated individuals generating measurable antibody-mediated neutralisation against HPV 45 at the peak response (one month post-3rd dose; i.e. month 7). Further outcome measures will be the proportion of vaccinated individuals generating measurable antibody-mediated neutralisation against non-vaccine HR HPV types and the geometric mean titres for each HPV type, by vaccine and sample type, at each time point. For proportions exact confidence intervals will be calculated. For titres data will be logged (base 10) and assuming normality on the log-scale 95% confidence intervals calculated. If for any reason data are clearly not normal then the 95% confidence interval may be calculated after excluding outliers (such as those individuals who fail to generate an acceptable immune response to vaccine-incorporated HPV types, 16 and 18). If a large proportion of the subjects fail to generate an acceptable response then it may not be possible to calculate geometric means.

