## **SAMPLE SIZE CALCULATION**

There are limited data regarding cross-reaction to non-vaccine HPV types. Clinical trials have not been powered to give precise estimates of protection against individual non-vaccine types, and where data have been reported these are commonly limited to cross-protection against the two next most common HPV types HPV 31 and HPV 45. Trials have estimated that protection against HPV 31 ranges from ~10% to 55% and against HPV 45 from ~60% to 90%; however, the confidence limits around these estimates are extremely wide (Paavonen et al., 2007; Brown et al., 2007).

The sample size estimates for this study are based on the assumption that the percentage of blood samples at month 7 with cross-reactive antibodies against HPV 31 will be between 10% and 55% and against HPV 45 between 25% and 90% (Giroglou et al., 2001; Combita et al., 2002; Smith et al., 2007). Recruitment of 200 participants in each arm of the study will enable

us to detect the percentage of cross reactive samples at month 7 within the limits shown in the following table.

| Cross reaction against: | Percentage of samples showing cross-reaction | Precision of estimate of the percentage of samples showing cross-reaction |
|-------------------------|----------------------------------------------|---------------------------------------------------------------------------|
| HPV 31                  | 10%                                          | +/- ~4%                                                                   |
|                         | 55%,                                         | +/- ~7%                                                                   |
| HPV 45                  | 25%                                          | +/- ~6%                                                                   |
|                         | 90%                                          | +/- ~4%                                                                   |

When comparing the two vaccines, the population percentages which give rise to an 80% or more chance that observed percentages in the two study arms will be found to be significantly different at the 5% level are shown below. For example, we would have an 80% chance of detecting as significantly different, 50% versus 35% cross-reactive antibodies in the two populations.

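### The titre analysis may drop girls who fail to respond to HPV 16/18, a post-randomisation exclusion that raises geometric mean titres and can distort the vaccine comparison in either direction

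*Protocol*

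**What the plan says.** The rule stands in the protocol under Statistical Methods, Brief description. The main outcome there is a proportion: "The main outcome will be the proportion of vaccinated individuals generating measurable antibody-mediated neutralisation against HPV 45" at month 7, with exact confidence intervals. The further outcomes include "the geometric mean titres for each HPV type, by vaccine and sample type, at each time point".

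The default for titres is: "For titres data will be logged (base 10) and assuming normality on the log-scale 95% confidence intervals calculated". The fallback opens with "If for any reason data are clearly not normal" and continues: "the 95% confidence interval may be calculated after excluding outliers (such as those individuals who fail to generate an acceptable immune response" to HPV 16 and 18). The section's only other provision is that geometric means may not be calculable if a large proportion fail to respond.

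The same section gives the primary purpose as measuring neutralising antibody against the vaccine types 16 and 18 as well as the related non-vaccine types. Section 2 (Objectives), item (ii), is "comparing the levels and patterns of cross-neutralisation induced by each vaccine to highlight potential differences in immunogenicity between the vaccines".

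**The concern.** Whether a girl responds to HPV 16/18 is known only after vaccination and is caused by the vaccine she was allocated. It is also one of the quantities the study sets out to measure. A girl who does not respond is a vaccine failure, not a faulty measurement, so calling her an outlier removes real information about the vaccine. An analysis restricted to responders compares two groups selected after randomisation, and randomisation no longer protects the comparison.

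At stake are the titre summaries for each vaccine and the comparison of titre levels between vaccines. The titres for non-vaccine types, which serve objective (ii), are included, because a girl dropped for her HPV 16/18 response is dropped from those summaries too.

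The fallback may also be reached easily. Sample Size Calculation assumes that 10-55% of month 7 samples cross-react with HPV 31 and 25-90% with HPV 45, which leaves 45-90% and 10-75% without cross-reaction. If those samples take a value at the assay limit, the log titres for these types cannot be normal. Removing HPV 16/18 non-responders would not cure that, since a girl can respond well to 16/18 and still not cross-react.

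**Working it through.** **The plan's own figures.** The only design figures concern proportions. With 200 per arm, 1.96 x sqrt(p(1-p)/200) gives 4.2%, 6.9%, 6.0% and 4.2% at p = 10%, 55%, 25% and 90%, matching the stated precision of about 4, 7, 6 and 4%. The detectable-difference table reproduces with a continuity-corrected two-sided 5% test at 80% power (201-202 per arm in all ten cells). None of this involves titres, so the exclusion rule leaves it untouched.

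**Inputs for titres.** From the protocol: 200 per arm and log10 titres. Assumed, because the documents give no values: non-response fraction f, a gap in log10 units between responders and non-responders, and the titre SD.

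**Step 1, one arm.** If responders have mean log10 titre m, the mean over all girls is m - f x gap. After exclusion it is m, so the GMT is multiplied by 10^(f x gap).

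| f | gap 1 | gap 2 | gap 3 |
|---|---|---|---|
| 2% | 1.05 | 1.10 | 1.15 |
| 5% | 1.12 | 1.26 | 1.41 |
| 10% | 1.26 | 1.58 | 2.00 |

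**Step 2, two arms with equal responder GMTs.** Take a responder GMT of 1000 (m = 3) and a gap of 2.
- 2% non-response: 10^(3 - 0.04) = 912. 10%: 10^(3 - 0.20) = 631. Ratio 912/631 = 1.45, which becomes 1.00 after exclusion.
- 1% versus 5%: 10^(0.04 x 2) = 1.20, becoming 1.00.
- 0.5% versus 1%: 10^(0.005 x 2) = 1.02, becoming 1.00.
- 5% versus 5%: both GMTs rise by 1.26 and the ratio stays 1.00.

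For power, take SD 0.5 log10 and 0% versus 10%. The variances are 0.25 and 0.25 + 0.1 x 0.9 x 4 = 0.61, so SE = sqrt(0.86/200) = 0.066 for a difference of 0.20. Power is 86% with all girls kept (89% in 4,000 simulations). After exclusion the rejection rate is 5%.

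**Step 3, the opposite direction.** Keep 2% versus 10% and a gap of 2, but let the 10% arm's responders have GMT 2000. Its all-girl GMT is 2000 x 10^(-0.2) = 1262, so the ratio is 1262/912 = 1.38. After exclusion it is 2000/1000 = 2.00.

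**Step 4, non-vaccine types.** With 10-55% of responders cross-reacting to HPV 31 and cross-reactors assumed 1 log10 above the below-limit value, the mean gap is only 0.10-0.55. Excluding 2% versus 10% then shifts the ratio by 10^(0.08 x 0.10) = 1.02 to 10^(0.08 x 0.55) = 1.11.

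**Step 5, the literal reading.** The sentence mentions only the interval. With 10% non-response, 180 of 200 kept and an assumed responder SD of 0.4, the interval is 3 +/- 1.96 x 0.4/sqrt(180) = 2.942 to 3.058, that is 874-1144, beside an all-girl GMT of 631. On this reading the GMT is not inflated, but it lies outside its own interval. Steps 1-4 apply instead if the GMT is recomputed on the same reduced set.

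**The case against.** The strongest reply is that this is a permissive, conditional fallback on a further outcome, in a section presented as a brief description, with full details deferred to the statistical analysis plan. Much of that stands. The main outcome and the other proportions keep every girl. Leaving the cut-off for an acceptable response, or the criterion for non-normality, to the analysis plan is ordinary practice and is not criticised here. What does not stand is that the analysis plan would settle the matter: the protocol does not merely omit a detail, it authorises this exclusion.

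It is also fair to say that the size rests wholly on assumed inputs, that small or balanced non-response does little harm, and that the effect is weaker for cross-reactive types.

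Three stronger readings are tempting and are not supported:
- A reader might infer that the rule always biases towards no difference. Step 3 shows the ratio growing from 1.38 to 2.00.
- A reader might infer that the HPV 16/18 response is what objective (ii) compares. That objective concerns cross-neutralisation; the vaccine-type response comes in through the stated primary purpose.
- A reader might infer that whoever holds the allocation list decides the exclusions. E. Randomisation says only that "A computerised block randomisation list will be produced by the Statistician at Cfl", and Data Analysis and Presentation names the Immunisation Department Statistician. The protocol does not say whether these are the same person or who would decide on exclusions.

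**Conclusion.** The rule is wrong as written and should be fixed, but it does not threaten the main result. It permits valid, randomised observations to be removed because of an outcome of the vaccine. If the GMT follows the interval onto the reduced set, any arm with non-responders has its GMT inflated, by 1.05 to 2.00 for f of 2-10% and gaps of 1-3 log10. The between-vaccine ratio is distorted only if non-response or its titre gap differs by arm, and the direction then depends on which arm's responders have the higher titres. With equal non-response and equal gaps the ratio is unchanged. If only the interval uses the reduced set, estimate and interval describe different girls. These magnitudes are illustrations on assumed non-response, gap and SD, not predictions for this trial.

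**What to change.** Delete the exclusion. Keep every randomised girl with a sample in all GMTs, GMT ratios and intervals. Give titres below the assay limit a pre-set value, or use a censored-data (Tobit) model, since values below the limit are a likely source of non-normality. If log titres are still not normal, use a bootstrap interval or a rank-based comparison on all girls. Show any responders-only result only as a labelled supplement, with the responder cut-off fixed in advance and the number removed given per arm.

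The cost is a few lines of protocol or analysis-plan wording. GMTs may be slightly lower and intervals slightly wider; recruitment, sampling and sample size do not change.

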## **SAMPLE SIZE CALCULATION**

There are limited data regarding cross-reaction to non-vaccine HPV types. Clinical trials have not been powered to give precise estimates of protection against individual non-vaccine types, and where data have been reported these are commonly limited to cross-protection against the two next most common HPV types HPV 31 and HPV 45. Trials have estimated that protection against HPV 31 ranges from ~10% to 55% and against HPV 45 from ~60% to 90%; however, the confidence limits around these estimates are extremely wide (Paavonen et al., 2007; Brown et al., 2007).

The sample size estimates for this study are based on the assumption that the percentage of blood samples at month 7 with cross-reactive antibodies against HPV 31 will be between 10% and 55% and against HPV 45 between 25% and 90% (Giroglou et al., 2001; Combita et al., 2002; Smith et al., 2007). Recruitment of 200 participants in each arm of the study will enable

us to detect the percentage of cross reactive samples at month 7 within the limits shown in the following table.

| Cross reaction against: | Percentage of samples showing cross-reaction | Precision of estimate of the percentage of samples showing cross-reaction |
|-------------------------|----------------------------------------------|---------------------------------------------------------------------------|
| HPV 31                  | 10%                                          | +/- ~4%                                                                   |
|                         | 55%,                                         | +/- ~7%                                                                   |
| HPV 45                  | 25%                                          | +/- ~6%                                                                   |
|                         | 90%                                          | +/- ~4%                                                                   |

When comparing the two vaccines, the population percentages which give rise to an 80% or more chance that observed percentages in the two study arms will be found to be significantly different at the 5% level are shown below. For example, we would have an 80% chance of detecting as significantly different, 50% versus 35% cross-reactive antibodies in the two populations.

| Percentage of samples with cross-reactive antibodies in Population 1 | Percentage of samples with cross-reactive antibodies in Population 2 (percentages that give rise to an 80% or more chance that the observed percentages in the two study arms will be found to be significantly different) |        |
|-----------------------------------------------------------------------------|-----------------------------------------------------------------------------------------------------------------------------------------------------------------------------------------------------------------------------------|--------|
| 10%                                                                         | ≤2.7%                                                                                                                                                                                                                             | ≥20.5% |
| 25%                                                                         | ≤13.5%                                                                                                                                                                                                                            | ≥38.5% |
| 50%                                                                         | ≤35.7%                                                                                                                                                                                                                            | ≥64.3% |
| 75%                                                                         | ≤61.5%                                                                                                                                                                                                                            | ≥86.5% |
| 90%                                                                         | ≤79.5%                                                                                                                                                                                                                            | ≥97.3% |

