## **SUBJECT ELIGIBILITY**

Inclusion criteria:

- Aged between 12 and 15 years at the time of the first immunisation
- Female
- No contraindications to vaccination as specified in the “Green Book” – Immunisation Against Infectious Disease, HMSO.
- Written informed consent obtained from parent or guardian of subject

Exclusion criteria

- Pregnant or become pregnant during the course of the trial (no contraindications to vaccination for those taking the contraceptive pill).
- Breast-feeding mothers
- Allergic to vaccine components

Deferral

- Subjects who have a fever (axillary temperature  $\geq 38^{\circ}\text{C}$ ), or have an acute infection will have injection delayed until resolution
- Not recommended in patients undergoing immunosuppressive therapy
- Not recommended for persons already undergoing vaccination as effect of co-immunisation with other vaccines has not been rigorously tested
- The JCVI (17 Oct 2007, 18 Jul 2008) advises that HPV vaccines and the Td/IPV school leaver booster (low dose diphtheria, tetanus and inactivated polio: Td/IPV) can be co-administered

Withdrawal criteria

- Subject becomes pregnant
- Subject or parent/guardian withdraws consent or lost to follow-up (HPA's SOP on Premature Withdrawal from a Study will be followed).

Girls aged 12 to 15 years will be recruited to this study. It is assumed that the immune response of these girls will not differ from that of girls vaccinated age 12-13 years as part of the routine HPV vaccination.

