## **NUMBER OF SUBJECTS AND DURATION OF STUDY**

A total of four hundred (400) subjects will be recruited through two centres: *North Hertfordshire* and *Gloucester*.

It is hoped that recruitment to the study will be completed in a 10-month timeframe. However, as with all adolescent studies, the recruitment rate depends on patient attitude and is largely unpredictable. Experience with previous studies in this age group with the number of Vaccine Research Nurses (VRNs) who will recruit to this study gives a recruitment estimate of 10-15 adolescents per week.

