#### **Blood**

Blood sampling will be in accordance with venepuncture SOP. No more than two attempts at venepuncture will be made. An anaesthetic cream (EMLA or Ametop) will be offered for use on the intended bleeding site to minimise discomfort. At least 5ml of blood and no more than 10 ml of blood will be taken at each sample collection point for serum generation. At month 7 (one month following the full regimen of GardasilTM or CervarixTM doses) an additional 30mls of

heparinised blood may be taken for the isolation and storage of peripheral blood mononuclear cells (PBMC; white blood cells).

The Vaccine Research Nurse (VRN) will stick an adhesive label bearing the subject's unique number onto each sample tube. She will also write the subject's initials on each label. Adhesive labels bearing the subject number will be packed with the samples and sent to the primary receiving laboratory, which will be:

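### The detectable-difference table counts all 200 girls recruited per arm as having a month-7 result, with no allowance for loss

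*Protocol*

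**What the plan says.** The protocol's SAMPLE SIZE CALCULATION attaches its figures to enrolment: "Recruitment of 200 participants in each arm of the study will enable" the precision listed in its first table. For the comparison of vaccines it then gives "the population percentages which give rise to an 80% or more chance" that the observed percentages "will be found to be significantly different at the 5% level are shown below". It does not say which test this refers to, or whether it is one- or two-sided.

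The section NUMBER OF SUBJECTS AND DURATION OF STUDY confirms that nothing is added on top: "A total of four hundred (400) subjects will be recruited through two centres", which is 2 x 200.

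The main outcome (STATISTICAL METHODS, Brief description) is a proportion measured at month 7, after three doses. The protocol foresees ways in which a recruited girl may have no such result. The withdrawal criteria under SUBJECT ELIGIBILITY include pregnancy and "Subject or parent/guardian withdraws consent or lost to follow-up". Under Collection and testing of samples, Blood, the rule is "No more than two attempts at venepuncture will be made". No loss rate is given anywhere.

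**The concern.** A power statement holds for the number of results analysed, not the number of girls enrolled. If the table needs 200 results per arm and 200 is also the recruitment target, the stated power of at least 80% assumes complete follow-up to month 7. A reader who later meets a non-significant vaccine comparison would judge it against a sensitivity somewhat better than the trial had. The sample size statement and its tables stand in the protocol, so this concerns what the protocol states and not detail deferred to the statistical analysis plan.

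**Working it through.** **Inputs from the protocol.** n = 200 per arm, 1:1; significance level 5%; power 80%; ten tabulated pairs, which form five mirror-image couples.

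**Assumptions.** A two-sided test (not stated, but it reproduces the table). Loss by month 7 of 5%, 10% or 15%, leaving 190, 180 or 170 per arm.

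**Formula.** With d = |p1 - p2| and p̄ = (p1 + p2)/2, power = Φ(z), where

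z = [(d - c)·√n - 1.96·√(2p̄(1 - p̄))] / √(p1(1 - p1) + p2(1 - p2)),

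with c = 1/n for the continuity-corrected version and c = 0 for the uncorrected one.

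**Step 1: reproduce the protocol's table.** Solving for 80% power at n = 200 with the correction gives 2.69/20.55, 13.49/38.50, 35.68/64.32, 61.50/86.51 and 79.45/97.31. The protocol prints 2.7/20.5, 13.5/38.5, 35.7/64.3, 61.5/86.5 and 79.5/97.3. The uncorrected formula does not fit: its 50% row would be 36.17/63.83. So the table was built on 200 evaluable girls per arm with a continuity correction.

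**Step 2: one pair by hand, 50% v 35.7%.** d = 0.143 and p̄ = 0.4285; the two square roots are 0.6998 and 0.6925.
- n = 200: z = [(0.143 - 0.005) x 14.142 - 1.96 x 0.6998]/0.6925 = (1.952 - 1.372)/0.6925 = 0.837, so power is 79.9%.
- n = 180: z = [(0.143 - 0.00556) x 13.416 - 1.372]/0.6925 = (1.844 - 1.372)/0.6925 = 0.682, so power is 75.2%.

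**Step 3: all pairs, power in %.**

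| Pair (mirror pair) | Corrected: 200 | 190 | 180 | 170 | Uncorrected: 200 | 190 | 180 | 170 |
|---|---|---|---|---|---|---|---|---|
| 10 v 2.7 (90 v 97.3) | 79.9 | 77.5 | 74.9 | 72.0 | 85.2 | 83.4 | 81.3 | 79.1 |
| 10 v 20.5 (90 v 79.5) | 79.7 | 77.4 | 74.9 | 72.2 | 83.4 | 81.5 | 79.4 | 77.1 |
| 25 v 13.5 (75 v 86.5) | 79.9 | 77.7 | 75.2 | 72.5 | 83.3 | 81.4 | 79.3 | 76.9 |
| 25 v 38.5 (75 v 61.5) | 80.0 | 77.8 | 75.3 | 72.7 | 82.9 | 80.9 | 78.8 | 76.5 |
| 50 v 35.7 (50 v 64.3) | 79.9 | 77.7 | 75.2 | 72.6 | 82.6 | 80.7 | 78.5 | 76.2 |

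Without the correction, the most demanding pair (50% v 35.7%) needs 187 per arm for 80%, a loss of 6.5% (13/200).

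**Step 4: check that the fall is not an artefact of the approximation.** Direct enumeration of Fisher's exact test for 50% v 35.7% gives 79.7% at 200, 75.0% at 180 and 73.6% at 170. For 25% v 13.5% it gives 80.3%, 76.0% and 73.0%.

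**The case against.** The strongest reply is that the protocol names no test and that the continuity correction is conservative. With an uncorrected chi-square test, formula power at 200 per arm is 82.6-85.2%, so there is built-in slack for a loss of about 6-7%. The protocol's own worked example, 50% v 35%, has 83.8% power at 200 even with the correction and keeps 80% down to about 183 per arm. The loss rates are assumptions, and withdrawal and venepuncture provisions are routine and say nothing about how many girls will be lost. Finally, the table is a grid of scenarios and not one powered hypothesis, and its limits shift little.

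Much of this stands, and it sets the size of the point. A reader might infer that the stated power fails as soon as a single girl is lost. The protocol does not support that: it is true on the method that built the table, but not if an uncorrected test is used, and not for the worked example. What remains is that neither the slack nor the loss is stated. By an assumed 10% loss, eight of the ten pairs are below 80% on either formula; by 15%, all ten are.

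A reader might also infer that the precision table is wrong, because it uses symmetric approximate margins while the statistical methods section says "For proportions exact confidence intervals will be calculated". That does not hold. The margins are given as approximate whole numbers (about 4, 7, 6 and 4 points at 10%, 55%, 25% and 90%). The average exact (Clopper-Pearson) half-widths at n = 200 are 4.4, 7.1, 6.2 and 4.4, which round to the same values. The symmetric margins at n = 180 (4.4, 7.3, 6.3 and 4.4) also still round to them. Only asymmetry is left: the exact interval at 10% runs -3.8/+5.0 points, and at 90% it runs -5.0/+3.8.

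**Conclusion.** The point holds for the detectable-difference table and is minor. That table treats every girl recruited as evaluable at month 7, although the protocol foresees losses before then. On the table's own method, power at the tabulated pairs is about 77-78%, 75% and 72-73% at 5%, 10% and 15% loss. With an uncorrected chi-square test it stays at or above 80% down to about 187 per arm; at 180, eight pairs have 78.5-79.4% and the other two 81.3%; at 170, all ten have 76-79%. These figures rest on a two-sided 5% test, equal loss in the two arms, and loss rates that are assumed because the protocol gives none. The precision table needs no correction.

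**What to change.** Keep 400 subjects. Restate the detectable-difference table for the number expected to be evaluable at month 7, and name the test and sidedness assumed. Continuity-corrected 80% limits are:

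| Population 1 | 190 per arm | 180 per arm | 170 per arm |
|---|---|---|---|
| 10% | ≤2.5 / ≥20.9 | ≤2.4 / ≥21.2 | ≤2.2 / ≥21.6 |
| 25% | ≤13.2 / ≥38.9 | ≤12.9 / ≥39.3 | ≤12.6 / ≥39.8 |
| 50% | ≤35.3 / ≥64.7 | ≤34.9 / ≥65.1 | ≤34.5 / ≥65.5 |
| 75% | ≤61.1 / ≥86.8 | ≤60.7 / ≥87.1 | ≤60.2 / ≥87.4 |
| 90% | ≤79.1 / ≥97.5 | ≤78.8 / ≥97.6 | ≤78.4 / ≥97.8 |

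The 180 column could serve as the main case, with 190 and 170 alongside, unless the sponsor has a better estimate of loss. The cost is one table and a sentence, with slightly less favourable stated figures: no limit moves by more than 0.8 of a point between 200 and 180 per arm. No extra subjects and no change of procedure are needed.
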